### 2.9. Interim analysis and monitoring

No interim analysis will be scheduled for this trial. However, the trial will be monitored by independent conductors to ensure that it is being conducted safely and in accordance with the protocol and that the data are being collected accurately. An audit will be conducted if the monitoring reveals significant violations of relevant rules and regulations or deviations from the protocol.

## 3. Discussion

The primary objective of this trial was to evaluate the usefulness of the TP measurement device for dysphagia in patients with HNC. The tongue plays a significant role in the oral stage of swallowing, and a decrease in TP may result in dysphagia.^[6–9]^ Therefore, maintaining TP will help prevent dysphagia; thus, better rehabilitation programs for dysphagia have been sought. Currently, a TP measurement device is generally used as a method of measuring TP.^[22]^ In the neurological field, the evaluation of dysphagia by a TP measurement device has already been established, and the correlation between lower TP and dysphagia has been clarified.^[5,18,19]^ However, the utility of assessing dysphagia using TP in patients with HNC has not yet been established. Despite that head and neck tumors often affect swallowing due to being in the oral cavity, pharynx, and larynx, there are currently limited methods for assessing dysphagia associated with HNC treatment.

In clinical practice, VE and VF are usually performed to evaluate dysphagia, and their utility has been established.^[23,24]^ However, these examinations carry a significant risk; therefore, they can cause AEs such as aspiration, pneumonia, and allergy to the contrast medium. Moreover, the VE and VF require practical clinical techniques. Therefore, this trial aimed to investigate the usefulness of evaluation by measuring TP for dysphagia related to HNC treatment.

In this trial, we evaluated the changes in TP affected by RT, since muscle damage by RT has already been reported and decreased TP could result in dysphagia in HNC patients.^[17]^ Thus, this study will include patients with OPC or HPC, in whom the tongue is exposed to radiation during treatment. As TP and swallowing function can be affected by the tumor itself, patients with oral cancer were excluded. Additionally, patients with laryngeal cancer were excluded because the radiation field for laryngeal cancer does not adequately include the tongue. The usefulness of TP measurement as the primary endpoint in HNC patients will be demonstrated. Additionally, the correlation between the change in TP and VE findings, as well as VF, will be analyzed as the secondary endpoint.

Measuring TP as a new method for evaluating swallowing function in HNC patients can provide several benefits. Firstly, the evaluation of swallowing function by measuring TP will enable the reduction of patient burden because the method of TP measurement is noninvasive, simpler, and safer than the VE and VF methods. Also, it allows easy assessment of swallowing function anywhere without the need for endoscopy or an X-ray device. Secondly, the TP measurement device provides objective and quantitative data that can be easily shared with medical staff to determine the extent of a patient dysphagia. Thirdly, objective swallowing data also helps in evaluating the effectiveness of RD. We expect that an easier evaluation of RD effectiveness will improve rehabilitation programs for dysphagia.

Overall, we expect this trial to contribute to the improvement of patients’ QOL.

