## 2. Methods

### 2.1. Study design

This clinical trial, currently ongoing at Nara Medical University Hospital, is a prospective, single-center, single-arm, non-blind, non-randomized clinical trial involving patients with oropharyngeal (OPC) or hypopharyngeal (HPC) cancer who undergo CRT or RT as the standard cancer treatment. Participants will undergo rehabilitation for dysphagia (RD) and several examinations, including TP measurement, VE, VF, cervical computed tomography, ultrasound examination, blood test, chest radiography, electrocardiogram, and respiratory function test. Moreover, AEs will be evaluated according to the Common Terminology Criteria for Adverse Events Version 5.0, as proposed by the National Cancer Institute.

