#### 2.5.5. Rehabilitation for dysphagia.

The participants will undergo RD to prevent or recover from functional decline in swallowing. RD was routinely scheduled as a protocol intervention during RT. The patients underwent the rehabilitation program in the morning and evening as follows:

Ice massage of the oral region (5 sets).Chin push-pull maneuver (10 seconds, 10 sets).Walking (3 minutes).

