### 2.6. Endpoints

#### 2.6.1. Primary endpoint.

The primary endpoint was the change in maximum TP value from baseline to 3 months after RT.

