#### 2.8.1. Primary endpoint.

The average and 95% CI of the changes in the maximum TP value from baseline 3 months after RT will be analyzed as the primary endpoint. Moreover, the ratio of patients with “Impossible” will be calculated.

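### The primary endpoint, a single-arm mean change in tongue pressure, cannot show the promised usefulness for dysphagia and cannot be attributed to radiotherapy alone

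*Protocol article*

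**What the plan says.** All references are to the protocol article.

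- **Objective (3. Discussion):** "The primary objective of this trial was to evaluate the usefulness of the TP measurement device for dysphagia in patients with HNC".
- **Promised conclusion (3. Discussion):** "The usefulness of TP measurement as the primary endpoint in HNC patients will be demonstrated".
- **Design (2.1):** a "prospective, single-center, single-arm, non-blind, non-randomized clinical trial".
- **Primary endpoint (2.6.1):** "The primary endpoint was the change in maximum TP value from baseline to 3 months after RT".
- **Primary analysis (2.8.1):** "The average and 95% CI of the changes in the maximum TP value from baseline 3 months after RT will be analyzed as the primary" (the sentence ends one word later). The same section adds the ratio of patients whose measurement is recorded as 'Impossible'. It gives no hypothesis, threshold or reference standard.
- **Attribution (3. Discussion):** "In this trial, we evaluated the changes in TP affected by RT".
- **Concurrent rehabilitation (2.5.5):** "The participants will undergo RD to prevent or recover from functional decline in swallowing", and "RD was routinely scheduled as a protocol intervention during RT", in a morning and evening programme.
- **Other treatment (2.5):** concurrent chemotherapy regimens are left open, and adjuvant and secondary treatments are allowed.
- **Analyses that link TP to dysphagia (2.8.2, all secondary):** a scatterplot and Pearson coefficient of TP against the Hyodo score, and the mean TP with its CI in patients classed as having dysphagia on VF.

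**The concern.** The objective asks whether TP is informative about dysphagia. The primary analysis asks how far TP moved on average. These are different questions, and the second does not answer the first: average TP may fall while the patients who lose TP are not those who develop dysphagia, or may stay flat while TP tracks swallowing closely from patient to patient.

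A second gap concerns cause. The Discussion describes the change as one produced by RT, but all participants are to have rehabilitation meant to prevent or reverse swallowing decline, and many may have chemotherapy. With no comparison group the parts cannot be separated.

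At stake is the final report. With no criterion, almost any primary result could be presented as the promised demonstration, while the analyses that bear on the question stay in the background and one of them is incomplete.

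**Working it through.** The article gives no figure for this point that could be reproduced. The check sets the sections side by side, with two small calculations.

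**1. What each planned quantity can show**

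| Quantity | Section | Bears on |
|---|---|---|
| Mean change in maximum TP, 95% CI | 2.8.1, primary | Whether TP changed |
| 'Impossible' ratio | 2.8.1, primary | Whether TP can be measured |
| Pearson r, TP against Hyodo | 2.8.2, secondary | Whether TP tracks the endoscopic findings |
| Mean TP in VF-dysphagia patients | 2.8.2, secondary | TP level in that group only |

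Only the last two rows involve dysphagia. The last names no non-dysphagia group, so by itself it cannot show that TP differs with dysphagia, although the Abstract and the Discussion both announce a correlation with VF.

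**2. Does the primary result depend on the link between TP and dysphagia?**

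Inputs: n = 40 (section 2.7) and SD of the change 15.0 (section 2.7, where the wording is garbled; reading 15.0 as the SD is an assumption). The mean change of −4 is assumed.

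Half-width of the 95% CI = t(0.975; 39) × SD/√n = 2.0227 × 15/√40 = 2.0227 × 2.372 = 4.80.

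In 4,000 simulated trials at each of two correlations between TP change and a dysphagia measure:

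| True correlation | Average mean change | Average half-width | Average sample correlation |
|---|---|---|---|
| 0 | −4.03 | 4.76 | 0.00 |
| −0.8 | −4.03 | 4.77 | −0.80 |

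A device that is unrelated to dysphagia and one that is strongly related give the same primary result. The mean and its CI carry no information on the association. The simulation holds the mean change fixed, so it does not address responsiveness.

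**3. What the planned secondary association can carry**

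Fisher 95% CI for r = tanh(atanh(r) ± 1.96/√(n − 3)). With n = 40, 1.96/√37 = 0.322.

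- r = −0.5: −0.70 to −0.22
- r = −0.3: −0.56 to 0.01

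The values of r are illustrative, and all 40 patients are assumed measured at one time point. A moderate association could be distinguished from zero, but only with a wide interval. Estimation language therefore suits the secondary analysis too.

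**4. What the change is a change under**

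Between baseline and 3 months after RT, patients have RT, possibly chemotherapy of any regimen (section 2.5), protocol rehabilitation during RT (section 2.5.5) and possibly adjuvant treatment (section 2.5). The Discussion also says that the tumour itself can affect TP, so tumour response is a further contributor. With one arm, only the sum is estimable.

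**The case against.** **The sentence is loosely worded.** Elsewhere the article speaks of investigating or evaluating usefulness, and the next sentence of the Discussion names the correlation with VE and VF as secondary. No decision rule ties a conclusion to the primary result. This is fair and makes the remedy mainly one of wording. It does not remove the mismatch: the softer sentences still set usefulness for dysphagia as the objective.

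**The primary result is not empty.** The Introduction argues that RT damages muscle and should lower TP, and that about half of patients develop dysphagia. On that reasoning a fall in TP is some evidence of responsiveness, and the 'Impossible' ratio, already in the primary analysis, speaks to feasibility. This stands. A reader might infer that no primary result could say anything about usefulness; the documents do not support that. Responsiveness remains partial evidence, because the primary analysis does not check whether swallowing worsened in the same patients, and the Introduction itself says there is no settled view of how RT changes TP.

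**The attribution rests on one phrase.** It sits in a paragraph explaining the choice of population. The endpoint is defined by time and the analysis is descriptive, and the single arm, the rehabilitation and the open chemotherapy are all disclosed. Being single-arm is therefore not an error. The phrase still needs correcting, because it gives the net change a cause that the design cannot isolate.

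**Rehabilitation.** A reader might infer that the trial claims to evaluate rehabilitation and lacks a comparator. It does not: the Discussion lists help in judging rehabilitation as a general benefit of TP data, and no endpoint addresses it. Nor do the documents give any figure for how far rehabilitation offsets a loss of TP, so no size of bias can be stated.

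**Conclusion.** The point holds as a mismatch between objective and primary endpoint and as an over-attribution to RT. The primary analysis supports a statement on the net 3-month change in maximum TP under RT or chemoradiotherapy plus protocol rehabilitation, and on measurability. It does not support a statement that TP reflects dysphagia.

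There is no numerical error to size. The half-width of about 4.80 TP units (n = 40, 15.0 read as the SD of the change) describes sampling error of the net change only. It covers neither the link to dysphagia nor the split between treatments.

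A reader might infer that the TP–VE/VF association must become a co-primary endpoint. The documents do not compel that: the trial is under way (section 2.1), and section 2.5.4 says that evaluation of VF is not yet established. It is enough that any conclusion on usefulness is tied to those analyses. The conclusion rests on the stated objective and endpoint, which analysis detail held in another document would not alter.

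**What to change.** 1. Restate the primary objective as estimating the change in maximum TP from baseline to 3 months in patients receiving RT or chemoradiotherapy plus protocol rehabilitation. Keep the 'Impossible' ratio in the primary analysis.
2. Delete the promise that usefulness will be demonstrated and the wording that attributes the change to RT alone. Say that the effects of RT, chemotherapy and rehabilitation cannot be separated in this design.
3. State that any conclusion on usefulness for dysphagia will rest on the planned secondary TP–Hyodo association and on TP compared between patients with and without VF dysphagia, each reported as an estimate with a 95% CI.
4. Add that VF comparison to section 2.8.2, which now summarises TP only in the dysphagia group. It depends on the rule that classes a patient as having VF dysphagia, so that rule should be settled before the data are analysed.

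**Cost:** a dated amendment of wording and one added comparison from data already collected, with no new patients, visits or procedures. No interim analysis is scheduled (section 2.9) and analysis follows data fixing (section 2.8), so the change can be made before results are seen. The downside is a less ambitious primary claim.
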